## Methods

### Design

ProKaSaRe is a prospective, multicentric observational study. All participants will be observed undergoing the usual structured, multidisciplinary rehabilitation program (Figure 1), which routinely includes a diagnostic assessment consisting of lung function measurements, a 6-minute walk test (6MWT) and various laboratory tests (described subsequently). As part of the study, patients with chronic sarcoidosis will be asked to answer several questionnaires at the beginning and at the end of the usual pulmonary rehabilitation program, as well as after 3, 6, and 12 months.

Ethical approval was granted by the Ethical Committee of the Hannover Medical School, Hannover, Germany (Nr 877).

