### Data Collection and Compilation

Data will be collected at 5 time points: T_0_-T_4_. Defined specific medical measurements and tests will be undertaken at the beginning and the end of the pulmonary rehabilitation program and a questionnaire concerning symptoms and HRQL will be provided at different points in time during the inpatient program and the follow-up period of 12 months (Table 1). Clinical data, sociodemographic data, medication and comorbidities, generic and illness-specific quality of life questionnaires and validated questionnaires documenting anxiety and depression, fatigue, and dyspnea will be monitored on admission at the start (T_0_) and at discharge from the rehabilitation program (T_1_) [22].

At T_0_, the core data will be compiled comprising sociomedical status, age, sex, body mass index (BMI), severity of sarcoidosis, and organ involvement and damage. Previous treatment will also be assessed.

The following clinical findings will be recorded by the doctors at the start (T_0_) and end (T_1_) of the rehabilitation program at each clinic using medical survey forms: lung function, gas exchange, physical fitness, and laboratory parameters. This includes the following measurements:

BMI [23]Lung function values: vital capacity (VC), residual volume (RV), total lung capacity (TLC), forced expiratory volume in 1 second (FEV_1_), specific airway resistance (sRaw), mouth occlusion pressure 0.1 seconds after onset of inspiration (P0.1), and maximal inspiratory mouth pressure (Pimax), and Tiffeneau-Index (the FEV_1_/VC ratio) [24]Gas exchange: blood gas analysis at rest and during exercise (25/50 Watt), transfer factor of the lung for carbon monoxide (Tlco) in a single breath (Tlco SB) and per alveolar volume (Tlco/Va)Physical fitness: 6MWT distance [25]Laboratory parameters: angiotensin-converting enzyme (ACE) and C-reactive protein (CRP)

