The psychological burden will be also documented at T_0_ using the Hospital Anxiety and Depression Scale (HADS-D) [26] and quality of life by the 36-item Short Form Health Survey (SF-36) and the St George’s Respiratory Questionnaire (SGRQ) [27]. The fatigue symptoms, which are often predominant in sarcoidosis, will be assessed by the Fatigue Assessment Scale (FAS) [28,29] and dyspnea will be measured using the Modified Medical Research Council Dyspnea Scale (mMRC)[30-32]. At 3, 6, and 12 months (T2, T3, and T4) after the rehabilitation program, the FAS, HADS-D, mMRC [30], SF-36, and SGRQ questionnaires will be completed again by the patients. Although the questionnaires at T_0_ and T_1_ will be submitted on site, the ones at T_2_ to T_4_ will be sent by post. The patients will be instructed to complete all questionnaires independently.

In addition, the patients’ views of the components of the individual rehabilitation programs and their perceived importance will be assessed at discharge (T_1_). Moreover, an evaluation of the program from the patients’ perspective will be included in the final questionnaire at T_4._

During the whole study, response shift will be assessed by a questionnaire comprising 5 questions illustrating the prospective hopes of the patient and the retrospective specific burden of disease on the patient.

Data collection by post at 3, 6, and 12 months after discharge from the clinics will proceed by means of standardized letters with enclosed questionnaires and stamped return envelopes. The completed questionnaires will be returned to the clinic at which the rehabilitation program was carried out. Nonresponding patients will be reminded to answer the questionnaire by an additional letter after 2 weeks. Further details and the distribution times of the questionnaires and the documentation of their components are shown in Figure 1 and Table 1.

**Table 1 table1:** Components of the questionnaires given at the beginning of rehabilitation (T_0_), at the end of rehabilitation (T_1_), and at 3, 6, and 12 months after the end of rehabilitation (T_2_, T_3_, and T_4_).

Component	Content
1. Core data	Age, sex
2. Diagnoses	How they were secured or their positive proof
3. Organ involvement and general symptoms	
4. Lung function tests	VC, RV, TLC, FEV_1_, sRaw, Tiffeneau-Index (each before/after bronchospasmolysis), P0.1, and Pimax (T_0_, T_1_)
5. Gas exchange	Resting and exercise blood gas analysis (25/50 Watt), Tlco SB, Tlco/VA, (T_0_, T_1_)

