### Sample Size Calculation and Statistics

Sample size calculation was carried out separately for both primary endpoints. Because both endpoints are equally important, the type I error was adjusted by Bonferroni multiplicity adjustment.

The minimal clinical difference for the health-related SGRQ corresponds to a change of 4 points in the score for patients with COPD. This value was also used in the planning of this study because no sarcoidosis-specific reference values were available. According to Jones [33], a 4-point difference between baseline values and follow-up data would indicate clinically relevant (long-term) effects. From the 95% confidence interval he observed in 97 patients, we estimated a standard deviation of 12.1. Assuming a 2-sided type I error of 2.5% and a power of 90%, the overall sample size required based on a paired *t* test would be 115 patients.

One estimated minimal clinical difference for the 6MWT distance corresponds to 26 m [34]. In absence of sarcoidosis-specific references, we suggest according to Marcon [35], a 6MWT distance of approximately 600 m (SD 80). Assuming a 2-sided type I error of 2.5% and a power of 90%, the overall sample size on the basis of a paired *t* test is 121. Thus, at least 121 patients are needed to test for both primary endpoints. To avoid a systematic “center bias,” each center should recruit at least 30 patients. Sample size calculations were performed using nQuery Advisor7.0.

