### Data Management and Statistical Analysis Procedures

Data management will be carried out by the Centre for Public Healthcare and statistical analysis by the Institute for Biostatistics at the Hannover Medical School.

The questionnaires will be anonymized using a clinic identifier and a consecutive patient number and will be digitized in duplicate at the Hannover Medical School and entered in Microsoft Access. The database tables will then be virtually superposed to identify differences between entries. When discrepancies are found, the data entry will be compared with that of the original questionnaire and corrected so that an accurate master dataset used for the descriptive analysis and the calculation of effect sizes will emerge.

The main analyses will be performed on the total study population. Missing values will be reported and not replaced initially. Changes in both primary endpoints between T_0_ and T_1_ will be evaluated with a paired *t* test and a 2-sided type I error of 2.5%.

Because ProKaSaRe is an exploratory study, for all analyses except for the primary analysis, *P* values will be assessed descriptively and considered to be of importance for *P*<.05. Therefore, no adjustment for multiplicity will be performed. Descriptive evaluation of clinical characteristics will be conducted. Changes from baseline for continuous data will be compared by paired *t* tests and given with 95% confidence intervals for the mean difference. Categorical parameters will be compared for T_1_ to T_4_ by chi-square test. Duration of sick leave and results of the sociomedical status documented by the physician (T_0_, T_1_) and by the patient (T_2_, T_3_, T_4_), the evaluation of rehabilitation from the patients´ perspective (T_1_) and patient-attributed value to the components of the individual rehabilitation program will be presented exploratively. For the questionnaires, a covariate analysis will be run using participating centers and baseline values as independent variables and the change from T_1_ and T_2_ to T_0_ as dependent variables. Further multivariate analyses are planned.

All statistical analyses will be conducted using the SAS 9.3 software (SAS Institute Inc, Cary, NC, USA) to show the impact of the rehabilitation program on the patients’ lives.

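### The chi-square test named for categorical parameters ignores that the same patients are measured at each visit, and its reference visit is unclear

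*Protocol article*

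**What the plan says.** In the protocol article, the section on data management and statistical analysis procedures gives one sentence to categorical data: "Categorical parameters will be compared for T_1_ to T_4_ by chi-square test". The sentence before it deals with continuous data: "Changes from baseline for continuous data will be compared by paired *t* tests and given with 95% confidence intervals for the mean difference". So pairing and a baseline reference are stated for continuous data, and neither is stated for categorical data.

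The design sections settle what is being compared. Under Design: "ProKaSaRe is a prospective, multicentric observational study"; no comparison group is described. Under Data Collection and Compilation: "Data will be collected at 5 time points: T_0_-T_4". The same section says that at 3, 6 and 12 months "the FAS, HADS-D, mMRC [30], SF-36, and SGRQ questionnaires will be completed again by the patients".

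The analysis section calls the study exploratory. Outside the primary analysis, P values are read descriptively, marked as important below .05, and not adjusted for multiplicity. The primary analysis is a paired t test of T0 against T1 for each of the two primary endpoints.

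**The concern.** With one cohort and no control arm, a comparison over T1 to T4 can only be a comparison between visits within the same patients. In a visit-by-category table each patient is then counted once per visit. The Pearson chi-square takes these counts as independent and computes the variance of a difference between visits without the covariance term. In a chronic disease, a patient's answers at two visits are very likely to be positively correlated. The computed variance is then too large and the P value too high.

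The plan uses P<.05 as its own marker of importance and wants the results to support the planning of a randomized trial. A categorical change of moderate size could therefore be reported as unimportant when a paired test on the same data would mark it.

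The sentence also starts at discharge (T1). Taken literally it describes the course after rehabilitation, whereas the article also asks about short- and long-term findings of the program, which need the admission value.

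**Working it through.** **Inputs.** From the article: n = 121 (Sample Size Calculation and Statistics) and the 5% marker for non-primary analyses. Assumed, because the article gives neither: within-patient correlation phi of 0.3 to 0.7 between binary responses, and the response proportions. Every patient is taken to answer at every visit.

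**The plan's own figure.** The article gives no calculation for categorical data. The 121 used here as sample size comes from the 6MWT and is reproduced: a difference of 26 m, SD 80 taken as the SD of the paired difference, two-sided 2.5% and 90% power need n = 121 by the noncentral t distribution (power 90.25%).

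**Size, two visits.** With equal proportions p, the true variance of the difference is 2p(1−p)(1−phi)/n; the chi-square uses 2p(1−p)/n. Its standard error is too large by the factor 1/√(1−phi), and the true size is 2·[1 − Φ(1.96/√(1−phi))].

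| phi | SE factor | effective critical value | true size, formula | true size, simulation | McNemar, simulation |
|---|---|---|---|---|---|
| 0.3 | 1.20 | 2.34 | 1.9% | 1.6–2.0% | about 5% |
| 0.5 | 1.41 | 2.77 | 0.56% | 0.4–0.7% | about 5% |
| 0.7 | 1.83 | 3.58 | 0.03% | 0.02–0.04% | about 5% |

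The simulations used a latent normal model with 5,000 to 20,000 runs per setting. At zero correlation the two tests agree (4.4–4.9% against 4.7–4.8%), so the loss comes from the correlation alone.

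**Size, one table over T1 to T4.** With equal correlation between all visits, the statistic behaves as (1−phi) times a chi-square with 3 degrees of freedom. The true size is P(χ²₃ > 7.815/(1−phi)):
- phi 0.3: cut-off 11.16, size 1.1% (simulated about 1%)
- phi 0.5: cut-off 15.63, size 0.14% (simulated 0.1–0.3%)
- phi 0.7: cut-off 26.05, size 0.001% (simulated 0)

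Cochran's Q, the repeated-measures counterpart, stays at 4.4–5.1% in the same simulations.

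**Power, 50% to 60%, two visits.** By the normal approximation at phi 0.5:
- True SE = √[(0.25 + 0.24 − 2·0.5·√(0.25·0.24))/121] = 0.0450.
- Chi-square SE = √(2·0.55·0.45/121) = 0.0640, so the observed difference must exceed 1.96·0.0640 = 0.1254.
- Chi-square power ≈ 1 − Φ((0.1254 − 0.10)/0.0450) = 29%.
- Paired power ≈ 1 − Φ(1.96 − 0.10/0.0450) = 60%.

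Simulated values:

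| phi (approx.) | chi-square | McNemar |
|---|---|---|
| 0.3 | 31% | 45% |
| 0.5 | 28% | 59% |
| 0.7 | 23% | 82% |

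**Larger shifts.** At phi of about 0.5 the chi-square finds 50% to 65% with 71% power and 50% to 70% with 95%, against 91% and 99% for McNemar.

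**Lower correlation.** At phi of about 0.2 the size is 2.7%, and power for 50% to 60% is 32% against 41%.

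**The case against.** **A paired test may be what was meant.** McNemar's test and Cochran's Q also use a chi-square reference distribution, and a journal article condenses. This is possible. But neither test is named, while the sentence just before says explicitly that its t tests are paired. An analyst who follows the text would run a Pearson test.

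**T0 may be implied.** A reader might infer that the plan leaves baseline out. The article does not prove that. Its Outcome Measurement section also lists SGRQ, FAS, HADS-D and SF-36 at T1 to T4, although the analysis section tests SGRQ and other continuous data as change from baseline. The phrase may be shorthand for each follow-up visit against admission. So this part stands as an ambiguity only. The independence problem remains under either reading: two visits in one case, four in the other.

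**Few parameters are affected.** A reader might extend the point to HADS or FAS categories and to work status. The article nowhere says that HADS or FAS will be categorized, and sociomedical status and sick leave are only to be presented exploratively. mMRC grade is the one plausible example. The abstract counts dyspnea scores as secondary, although the Outcome Measurement list does not repeat them.

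**The consequences are limited.** A reader might infer that real changes will usually be missed, or that false positives will rise. Neither follows. The test is conservative, the proportions reported at each visit stay correct, and large shifts are still found. These analyses are exploratory and their P values descriptive. This objection stands and sets the grade.

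**Conclusion.** The named test does not fit the design and gives P values that are too large when answers within a patient are positively correlated. At the 5% marker with two visits, the true size falls to about 1.6–2% at phi 0.3, 0.4–0.7% at phi 0.5 and 0.03% at phi 0.7. Against McNemar's test, the power lost for a shift from 50% to 60% is about 14, 31 and 59 percentage points (45−31, 59−28, 82−23). These figures rest on assumed correlations and proportions, binary responses, n = 121 and complete answers at both visits. The direction of the error needs only positive correlation.

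Whether change from admission is tested for categorical data cannot be told from the sentence.

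The grade is should-fix. The two primary paired t tests, the sample size and the data collection are unaffected, and a must-fix grade would not match the descriptive role of these P values.

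**What to change.** Replace the sentence with: *Categorical parameters at each of T1 to T4 will be compared with T0 by McNemar's test (binary) or by Bowker's test or the Wilcoxon signed-rank test (multi-category or ordinal).* For an ordered scale such as mMRC grade, the signed-rank test is the natural choice of the last two.

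This names both the paired method and the reference visit. A GEE or mixed model over T0 to T4 with patient as cluster is optional. It would describe the whole course and also use patients who miss a postal questionnaire, whereas the paired tests use only patients with both visits.

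The cost is one sentence and different SAS procedure calls. No new data are needed.

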#### Data Quality Check

The planned double data entry and the possibility of referring to the clinical files in case of runaway values and spikes concerning lung function, gas exchange, and laboratory parameters should ensure high data quality.

### Intervention

The intervention is an inpatient rehabilitation program lasting 3 weeks. The program is modular, with obligatory and optional components. All components are available at all study centers (Textbox 1). The reasons for choosing these interventions rather than others is described briefly in the following.

Rehabilitation is oriented according to the nature and extent of the difficulties resulting from single (sarcoidosis) or multiple illnesses (comorbidities) that the individual patient suffers that affect professional and daily life. According to these disabilities and functional deficiencies (as defined by the rehabilitation admission tests and assessments), the therapy components are individually and quantitatively adapted.

Components of the (usual) rehabilitation program carried out by all participating sites in ProKaSaRe.Obligatory componentsSpecialist confirmation of diagnosis and checks of current medication.Endurance training: from 3 to 5 training sessions per week at approximately 60-80% of maximum capacity (walking, power walking, or cycle ergometer).Strength training: 3 medical training therapy sessions per week.Respiratory physiotherapy: at least three group sessions per week and at least two individual respiratory therapy sessions during the rehabilitation program.Patient education: modular sarcoidosis education program.Optional componentsInspiratory muscle training: at least five sessions (each 30 minutes) per week, starting at 30% PI_max_. Sessions supervised at least once a week.Relaxation treatment: autogenic training or progressive muscle relaxation.Social counseling.Nutrition counseling.Psychological individual and group therapy.Structured smoking cessation.Ergotherapy and advice on devices and equipment.Patient education: additional courses (eg, long-term oxygen therapy training).

#### Obligatory Components

Endurance training is intended to improve performance, shortness of breath, mood, and quality of life. It also compensates for cortisone adverse effects, such as osteoporosis, muscle degeneration, weight gain, diabetes, and high blood pressure [15,48,49], allowing improvement in activities of daily life as defined by the International Classification of Functioning, Disability and Health (ICF) [50]. Cortisone may also affect the mood, sometimes toward depression or irritability.

Respiratory physiotherapy supports the learning of coughing techniques, positions which make breathing easier, handling shortness of breath on exertion, stretching positions to maintain the flexibility of the bony thorax (particularly with fibrosis), correct breathing techniques, and improvements in the respiratory muscles.

Patient education provides the sick person with information on the clinical picture, helps them to cope with their illness, and deal with all the information on adverse effects of their therapies (eg, cortisone). It puts sarcoidosis into perspective and helps to reduce anxiety and depression by generating feelings of informed safety. It explains the reasons for and frequencies of check-ups and helps patients to differentiate between required and unnecessary diagnostic tests. Alternative therapies and their evaluation with respect to sarcoidosis treatment could be addressed. Finally, it generates opportunities for strong interaction and bonding with other patients.

#### Optional Components

Inspiratory muscle training is known to improve the strength of respiratory muscles [51]. Relaxation treatment helps to reduce the symptoms of disquiet, stress, and anxiety.

Social counseling provides advice relating to societal participation, level of disability, severe disability, career reintegration according to social statutes and the ICF, taking early retirement, and applying for benefits, etc [49,52,53].

Nutrition counseling will also be offered on demand, particularly with reference to the adverse effects of cortisone therapy, such as osteoporosis, increased weight, diabetes, and high blood pressure, including counseling on the subject of a healthy diet.

Psychological individual and group therapy will be offered when needed. Individual therapy includes counseling and advice when anxiety, depression, insecurity, and problems coming to terms with the illness occur due to the chronic nature of the illness [54]. Structured smoking cessation will be offered to all smokers. Ergotherapy and advice on devices and equipment will be occasionally appropriate as part of physiotherapy.

## Results

Funding was obtained on October 12, 2010; enrollment began on January 15, 2011 and was completed by January 14, 2012. Results are anticipated late summer 2015.

## Discussion

Sarcoidosis is a systemic disease of unknown etiology that can affect all organs. Therefore, it presents a heterogeneous clinical picture associated with multiple comorbidities. It can occur at any age with a peak between the ages of 20 and 40, with women having a higher frequency of illness than men do, and it can show a chronic or chronic-relapsing pattern. Significant functional limitations include reduced quality of life and an often-debilitating fatigue that hinders the patients’ participation in “normal” daily life. Sarcoidosis is often insufficiently treatable by drugs alone. Can rehabilitation slow down disease progression and accelerate recovery and return to employment? ProKaSaRe seeks to find out whether and to what extent a rehabilitative intervention can substantially contribute to the care of patients with sarcoidosis.

This paper outlines the rationale and design for a prospective, “real-life” multicenter study using obligatory and optional components administered by a multiprofessional team. The aim is to explore the effects of a 3-week inpatient multiprofessional pulmonary rehabilitation program. ProKaSaRe will supply lacking evidence as to the degree to which a training-based multimodal rehabilitation can produce or enhance a significant and sustained improvement to HRQL, physical fitness, and psychological distress. This is particularly relevant in light of the myasthenia and fatigue mentioned previously, which are common symptoms of sarcoidosis.

During 2011, 929 sarcoidosis patients were admitted for inpatient rehabilitation in Germany [55]. We plan to enroll at least 121 consecutive patients within ProKaSaRe, a number that will encompass almost a seventh of all patients undergoing rehabilitation for sarcoidosis in Germany during the year of the study. By using a recruitment time of 12 months, seasonal influences will be excluded, which adds to the validity of the findings.

ProKaSaRe will help to define the patient group currently being referred for pulmonary rehabilitation in Germany, while simultaneously documenting the effect of pulmonary rehabilitation in terms of clinically relevant outcome parameters, if any.

The inpatient rehabilitation that will be assessed consists of a clearly defined set of components developed and approved by experts in the field accredited by the German health system following assessment of their professional development and experience as heads of specialized centers. The detailed agreed-upon choice of components and the broad assessment of HRQL reflecting the subsequent patients’ reaction to their chosen and advised measures represent the strengths of ProKaSaRe.

Scientists and physicians tend to define therapeutic success by only the improvement in pulmonary function, whereas patients equate successful treatment with tangible effects in their daily lives and an improved sense of well-being. This latter ultimately determines long-lasting positive effects, as stated by the ICF [50]. For this reason, both measurements (clinical data and patients’ self-evaluation) are necessary to form a balanced picture of pulmonary rehabilitation outcomes.

Although ProKaSaRe could contain some bias because it assesses only the sarcoidosis population willing to undergo pulmonary rehabilitation and is not a RCT, it is nevertheless a real-life study. Therefore, it is likely that the results generated in ProKaSaRe will be highly generalizable.

In contrast to studies focusing on single nonpharmaceutical components of rehabilitation programs, ProKaSaRe considers the entirety of the pulmonary rehabilitation program. The participants represent a real-life sample of sarcoidosis patients rather than a selected subpopulation thereby adding to the importance of the findings for medical and economical deliberations.

If the results of ProKaSaRe show effectiveness of the rehabilitation over a long period of time, rehabilitation as documented by the study would offer perspective and justified hope to concerned patients and their families and also evidence to stakeholders in the health care system. The documented efficacy of pulmonary rehabilitation for sarcoidosis patients will fill a gap in the reference literature used to develop guidelines and efficient long-lasting treatment procedures. It may establish rehabilitation as an irreplaceable and necessary additional therapeutic option for sarcoidosis, with highly relevant outcomes, which is only effective in its entirety and is more than the sum of single administrated components.

Depending on the outcome of ProKaSaRe, an RCT will be planned to advance knowledge and funding will be applied for. The definition of patient groups to which rehabilitation offers the greatest benefit and the estimation of the financial savings by the prescription of a rehabilitation program would be the next topics to be investigated.

